### Participant timeline {13}

Table 2 Shows a schematic of the participant timeline.

**Table 2 Tab2:** Timeline for data collection (SPIRIT Figure)

	Screening	Allocation	Post-allocation			Close-out	
TIMEPOINT	Pre-intervention		Intervention	Closed reduction & immobilisation	Post-intervention	Discharge from ED	Post Discharge from ED
ENROLMENT:							
Eligibility screen	X						
Informed consent	X						
Participant demographics	X						
Randomisation		X					
INTERVENTIONS:							
*UGSCB*			X				
*BB*			X				
Closed reduction & immobilisation				X			
ASSESSMENTS:							
Pain VAS during closed reduction^a^				X			
Baseline Pain VAS	X						
Pain VAS prior to discharge					X		
Patient satisfaction VAS					X		
ED length of stay						X	
Opioid use						X	
Adverse events or complications						X	
Adjunct therapy or treatment failures						X	
Number of sedations and techniques used in ED						X	
Number of inpatient transfers, subsequent sedations, or operations							X

*Abbreviations*: *UGSCB* Ultrasound-guided supraclavicular block, *BB* Bier block, *VAS* Visual analogue scale, *ED* Emergency department

^a^Primary outcome

### Sample size {14}

Sample size calculations were based upon a hypothesis of non-inferiority of UGSCB compared to BB for the primary outcome measure of maximal pain during closed reduction. Sample size calculations were based upon approximation to the normal distribution [14] using previous pain VAS scores reported by Kukreja et al. [9] and Beck et al. [15]. A non-inferiority margin of 20 mm was selected for power calculation. This was based on a previous study [15] that compared Bier block to a periosteal block (i.e., injection of local anaesthetic at the fracture site) for closed reduction of distal radius fractures. That study showed median pain VAS during closed reduction was 5 mm for Bier block and 26 mm for periosteal block (i.e., difference of 21 mm on pain VAS, which was rounded to 20 mm), but both techniques provided adequate anesthesia for tolerance of closed reduction procedure. Thus, a non-inferiority margin of 20 mm difference in mean VAS score was selected for the trial.

Assuming a non-inferiority margin of 20 mm difference in the mean VAS pain score, expected standard deviation of 30 mm [9], alpha 0.025 and a power of 80%, we would require primary outcome data for 72 participants. Allowing for an attrition rate of 5%, we estimate that we would require a total sample size of 76 participants for the study (i.e. 38 participants per group).

### Recruitment {15}

To maximise participant recruitment, we will hold several training sessions to have emergency physicians trained in both UGSCB and BB available at the time of patient recruitment and randomisation. We will also educate all ED staff regarding the eligibility criteria for the trial. Coverage will be available during day and evening shifts, with variable coverage at night depending on the senior doctor rostered.

## Assignment of interventions: allocation

### Sequence generation {16a}

Randomisation will be concealed by using the Griffith Randomisation Service (http://randomisation.griffith.edu.au/) to randomise participants to either UGSCB or BB. This involves a centralised, computer-generated algorithm with block randomisation performed in a 1:1 ratio to ensure equal numbers in each group.

### Concealment mechanism {16b}

This is already described in 16a.

### Implementation {16c}

Participants eligible for the research trial will be enrolled by either the research investigator, research assistant or treating clinician. Allocation of participants to either UGSCB or BB will be performed using the Griffith Randomisation Service.

## Assignment of interventions: blinding

### Who will be blinded {17a}

The trial will be conducted as an open-label study, with participants and treating clinicians aware of the group allocation. Outcome assessors and data analysts will be masked to the group allocation when analysing the primary and secondary outcomes.

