### Outcomes {12}

The primary outcome of the study will be the maximal level of pain experienced during closed reduction of the injured part, as reported by the participant on a 10 cm visual analogue scale (VAS) immediately after completion of the closed reduction procedure. The patient will be asked by the research investigator, research assistant or treating clinician to mark their pain on a VAS scale printed on paper anchored with “no pain” at 0 cm and “pain as bad as it could possibly be” at 10 cm. The 10 cm VAS has been demonstrated previously to be valid and reliable for participant-reported pain [12].

Secondary outcome measures will include:Baseline pain: Participant reported pain will be measured using a 10 cm VAS immediately prior to the commencement of either UGSCB or BB. Any analgesia administered prior to the procedure will be compared between groups to ensure that they are similar.Pain at one hour post-procedure: Participant reported pain at one hour post procedure (or just prior to discharge if under an hour) will be measured using a 10 cm VAS.Patient satisfaction will be measured using a 10 cm VAS satisfaction scale anchored with “extremely dissatisfied” at 0 cm and “extremely satisfied” at 10 cm. This will be measured one hour post procedure (or just prior to discharge if under an hour). The patient satisfaction VAS has been validated to be a reliable tool to evaluate patient satisfaction [13].ED length of stay: the time (minutes) from triage to readiness to be discharged from the ED, will be obtained from the electronic medical record.Analgesia: The total opioid use including those given by the ambulance service pre-hospital and those administered in the ED will be recorded. Total opioid use will be converted to oral morphine milligram equivalent using Australian and New Zealand College of Anaesthetists Faculty of Pain Medicine opioid calculator (http://www.opioidcalculator.com.au).Management: The number of sedations and techniques required in ED, the number of inpatient transfers, and the number of manipulations or operations at another hospital will be compared between groups.Adverse events/complications: Any adverse events experienced by the participant or noted by the treating clinician will be recorded. We will also contact the participant via email 24–72 h after discharge from the ED to evaluate any adverse events post-discharge.Adjunct therapies or treatment failure for UGSCB and BB will also be compared between the two groups.

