## Data collection and management

### Plans for assessment and collection of outcomes {18a}

Research staff or trained clinicians will enter the data onto a paper based clinical research form, which was designed by the research team. Once data collection is completed for each participant, the data will then be entered into an electronic database (REDCap), which has built-in checks to ensure that the data collected is complete. The database which will be later assessed by a research member blinded to the group allocation.

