## Oversight and monitoring

### Composition of the coordinating centre and trial steering committee {5d}

The coordinating centre is the ED at Redland Hospital in Brisbane, Australia. The trial steering committee consists of the principal investigator (HT) and co-investigations (CT, MT, PJ and PS), who are responsible for participant recruitment, execution of the research protocol, data collection and entry. All members of the trial steering committee are Good Clinical Practice certified.

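### Outcome assessors are listed as masked, but no outcome is described as being obtained by a masked person; only the later database review and the analysis are masked

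*Protocol article*

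**What the plan says.** The section Who will be blinded {17a} makes two statements in succession. The first is "The trial will be conducted as an open-label study, with participants and treating clinicians aware of the group allocation". The second is "Outcome assessors and data analysts will be masked to the group allocation when analysing the primary and secondary outcomes".

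Other sections show who produces each outcome:

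- **Primary outcome** (Outcomes {12}): maximal pain "as reported by the participant on a 10 cm visual analogue scale (VAS) immediately after completion of the closed reduction procedure". On collection: "The patient will be asked by the research investigator, research assistant or treating clinician to mark their pain on a VAS scale printed on paper".
- **Other participant ratings** (Outcomes {12}): baseline pain and one-hour pain are also participant-reported VAS scores, and "Patient satisfaction will be measured using a 10 cm VAS satisfaction scale". The article does not say who obtains these marks.
- **Harms** (Outcomes {12}): "Any adverse events experienced by the participant or noted by the treating clinician will be recorded", with an email to participants after discharge.
- **Block adequacy and failure** (Bier block, under {6b}; Intervention description {11a}; Criteria for discontinuing or modifying {11b}): the treating clinician judges adequacy in both arms and chooses what to do if the participant cannot tolerate the reduction.
- **Data recording** ({18a}): "Research staff or trained clinicians will enter the data onto a paper based clinical research form". A research member blinded to allocation assesses the database later.
- **Investigators' roles** ({5d}): the steering committee members are those "who are responsible for participant recruitment, execution of the research protocol, data collection and entry".

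**The concern.** Under the reporting item on who is blinded, outcome assessors are named separately from data analysts. A reader will take this to mean that the outcomes are assessed without knowledge of allocation. For the primary outcome the assessor is the participant, whom the preceding sentence declares aware of allocation. The person asking for the mark may be the treating clinician, whom the same sentence also declares aware.

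This matters because the endpoint is subjective and a single non-inferiority conclusion rests on it. Knowledge of treatment, or the identity of the person asking, can move a self-rated score. A shift favouring the supraclavicular block makes a false claim of non-inferiority more likely; a shift against it makes a true claim harder to reach. Masking the database reviewer or analyst cannot correct a score already fixed on paper.

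**Working it through.** **Step 1: who assesses, and is that person masked?**

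| Outcome or step | Who produces it | Masking status in the article |
|---|---|---|
| Procedural, baseline and one-hour pain; satisfaction | Participant | Stated to be aware |
| Request for the primary mark | Investigator, research assistant or treating clinician | Clinician stated to be aware; no masking stated for the others at the bedside |
| Block adequacy; response to failure | Treating clinician | Stated to be aware |
| Adverse events | Participant or treating clinician | Both stated to be aware |
| Paper research form | Research staff or trained clinicians | No masking stated |
| ED length of stay | Electronic medical record | Not a bedside rating |
| Later database review | Blinded research member | Masked |
| Statistical analysis | Data analysts | Masked |

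The masked steps come after the scores exist.

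**Step 2: reproduce the protocol's sample size.** Inputs from Sample size {14}: margin 20 mm, SD 30 mm, alpha 0.025 (read as one-sided, which matches the 95% confidence interval rule in {20a}), power 80%, true difference taken as 0.

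n per arm = 2 × (1.960 + 0.842)² × 30² / 20² = 35.3, rounded up to 36, so 72 in total. With 5% attrition, 72 / 0.95 = 75.8, rounded up to 76. Both stated figures reproduce.

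**Step 3: what a reporting shift would do.**

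SE of the difference = 30 × √(2/36) = 7.07 mm.

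Let b be the size of a shift in the mean difference caused by unmasked reporting. The documents give no value for b; those below are assumptions.

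- Shift favouring the supraclavicular block, true difference equal to the margin: P(non-inferiority declared) = Φ(b/7.07 − 1.96).
- Shift against it, true difference 0: power = Φ((20 − b)/7.07 − 1.96).

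| Assumed shift b | False non-inferiority (shift in favour) | Power (shift against) |
|---|---|---|
| 0 mm | 2.5% | 80.7% |
| 2 mm | 4.7% | 72.1% |
| 5 mm | 10.5% | 56.4% |
| 10 mm | 29.3% | 29.3% |

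For b = 5: Φ(0.707 − 1.960) = Φ(−1.253) = 0.105, and Φ(15/7.07 − 1.960) = Φ(0.161) = 0.564.

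These figures describe unmasked reporting as a whole. The share due to who obtains the mark cannot be separated from the documents.

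**The case against.** The best defence is that the sentence limits masking to the time of analysis, and that {18a} describes a matching step, the blinded database review. The open-label design is declared in the title and repeated, and the participant-reported nature of the VAS is plain. On this view the fault is one loose term. Much of this stands. A reader might infer that the trial has no masking at all; the documents do not support that, because masked review and analysis are planned. The defence still does not explain who the masked outcome assessors are, since the article describes none at the point where outcomes are obtained.

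Three other stronger readings also fail:

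- **The operator collects the pain score.** The article does not say so. The treating clinician is never defined as the person who did the block. Nothing excludes it either.
- **Research staff at the bedside are unmasked.** This is a strong inference from their roles and from two visibly different procedures, but only participants and treating clinicians are expressly described as aware.
- **The bias favours the new block because the team promotes it.** The background calls its effectiveness in the ED unclear, and {15} plans physicians trained in both techniques. The text fixes no direction.

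Safeguards exist too. The participant marks an anchored paper scale, listed adverse events are checked systematically with an open question added, and inadequate anaesthesia is tied to inability to tolerate the reduction. These make recording more consistent but do not mask anyone.

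Finally, rewording the blinding section alone changes no result, and participants stay unmasked whatever is done. That is correct, and it is why the fix also addresses how the marks are obtained.

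**Conclusion.** The point holds as an inconsistency about who is masked, together with an avoidable weakness in how the primary outcome is collected. Pain and satisfaction are rated by participants who know their allocation. The primary mark may be requested by a clinician who knows it, and block adequacy and bedside harms are judged or noted by that clinician.

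The possible effect is material if a shift occurs: at an assumed 5 mm, false non-inferiority at the margin is about 10.5% in place of 2.5%, or power at no difference is about 56% in place of 81%, depending on direction. This rests on the protocol's SD of 30 mm, 36 analysed per arm, a normal approximation and the assumed shift. It shows how sensitive the conclusion is to reporting bias and is no estimate of the bias in this trial. The sample size itself is correct, and the open-label design is not in question.

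**What to change.** 1. In Who will be blinded {17a}, state that participant-reported outcomes, block failure and adverse events are assessed without masking, and that only the database review and the statistical analysis are masked.
2. In Outcomes {12}, state that the person who performed the block does not obtain the pain or satisfaction VAS. The participant marks the paper scale privately after a fixed, scripted question and hands it, folded or sealed, to any staff member.

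The cost is two wording changes, a short script and envelopes. No additional assessor is needed, because the participant completes and seals the scale alone. There is a small logistical burden on shifts with limited coverage; {15} notes that night coverage varies. The reported masking will look less favourable, but it will be accurate. Treatment, sample size and analysis are unchanged. The change removes only the part of any bias that comes from who obtains the mark; the part that comes from participants knowing their allocation remains and should be acknowledged when the results are reported.

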### Procedure for unblinding if needed {17b}

There will be no unblinding required until the completion of the trial.

## Data collection and management

### Plans for assessment and collection of outcomes {18a}

Research staff or trained clinicians will enter the data onto a paper based clinical research form, which was designed by the research team. Once data collection is completed for each participant, the data will then be entered into an electronic database (REDCap), which has built-in checks to ensure that the data collected is complete. The database which will be later assessed by a research member blinded to the group allocation.

### Plans to promote participant retention and complete follow-up {18b}

The collection of primary and secondary outcome data will occur before, during and after the allocated intervention and closed reduction during the index ED presentation, as well as from routine medical records obtained during that presentation. As data is obtained during the same clinical event as participant recruitment, rates of attrition are expected to be low. Should a participant elect to withdraw from the study, no further additional information will be collected, although non-identifiable data such as pain scores already collected will be retained to ensure the result of the study can be measured.

### Data management {19}

Data generated by the project staff will be stored in a secure password protected internet-based database (REDCap) with access only by the research investigators involved in the study. Paper-based data will be kept in a locked cabinet in the office of the principal investigator. We will maintain the data for at least 15 years as recommended by the National Health and Medical Research Council of Australia. After this period of time, digital data will be destroyed by deleting the database and paper records will be shredded.

### Confidentiality {27}

Each participant will be allocated a unique identification code in order to protect their identity. Any data collected will then be recorded with respect to this code. No individual data will be reported in the trial.

### Plans for collection, laboratory evaluation and storage of biological specimens for genetic or molecular analysis in this trial/future use {33}

This study does not involve collection of biological specimens.

## Statistical methods

### Statistical methods for primary and secondary outcomes {20a}

Group data will be used for data and statistical analysis. Data will be summarised as mean (standard deviation) or median (interquartile range) for continuous variables, depending on the normality of their distribution, and as frequency (percentage) for categorical variables. The primary outcome of pain intensity during the procedure will be assessed as a non-inferiority hypothesis using data from the 10 cm VAS tool. The between-group difference in pain intensity will be assessed using linear regression modelling with group allocation (UGSCB vs BB) included as a main effect. A conclusion of non-inferiority will be determined if the 95% confidence interval for the between-group difference in mean maximal pain is entirely below the non-inferiority margin. Analysis will be performed on an intention-to-treat basis, with a per-protocol analysis of the primary outcome also included as a key secondary finding.

For analysis of other secondary outcomes, linear regression modelling will be used to compare continuous outcome data, including between-group difference in patient satisfaction on the 10 cm VAS satisfaction scale and total opiate dose in mg of morphine equivalent. Difference in median procedural time and ED length of stay will be compared using median regression. Odds of dichotomous outcomes will be compared using logistic regression modelling. Formal adjustment for multiplicity will not be performed. Analysis will be performed on Stata (StataCorp, Texas USA), v14.2 or later.

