### Trial design {8}

SUPERB is an open-label, single-site, non-inferiority randomised controlled trial (RCT), with a 1:1 allocation ratio. The protocol adheres to the Standard Protocol Items: Recommendations for Interventional Trials (SPIRIT) Statement.

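### Free improvement: the primary model names only group allocation, and adding baseline pain VAS could narrow the deciding confidence interval once its timing is settled before allocation

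*Protocol article*

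**What the plan says.** Statistical methods {20a} assesses the primary outcome by "linear regression modelling with group allocation (UGSCB vs BB) included as a main effect". No other model term is named there or elsewhere in the article. Non-inferiority is concluded if the "95% confidence interval for the between-group difference in mean maximal pain is entirely below the non-inferiority margin".

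Sample size {14} matches an unadjusted model: "Assuming a non-inferiority margin of 20 mm difference in the mean VAS pain score", "expected standard deviation of 30 mm", "alpha 0.025 and a power of 80" per cent. This leads to 72 participants with primary outcome data and 76 in total.

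Baseline pain appears in three roles:

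- The abstract and Outcomes {12} list it among the secondary outcomes. Objectives {7} does not include it among the secondary objectives.
- Outcomes {12} times it just before the block: "Participant reported pain will be measured using a 10 cm VAS immediately prior to the commencement of either UGSCB or BB".
- Table 2 in Participant timeline {13} marks the row "Baseline Pain VAS" in the Screening column, to the left of the separate Allocation column.

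**The concern.** A score on the same scale as the primary outcome, taken before the block, is the natural covariate for a pain trial. If it predicts pain during reduction, putting it in the model lowers the residual variance and narrows the interval whose upper bound decides non-inferiority. It also removes the effect of a chance difference in baseline pain, which matters more with about 36 analysed per arm than in a large trial. The plan collects this variable but does not say that it will be used in this way.

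Two details bear on how useful it would be. First, baseline pain is filed as an outcome although the block cannot affect it. Compared between arms as an outcome, it would show only chance imbalance, provided it was recorded before allocation was known. Second, the two stated timings fall on different sides of allocation. The block has to be assigned before it starts, so the wording in Outcomes {12} most naturally means after randomisation. The trial is open-label ({17a}), so a participant scoring pain then may already know which block is coming. A self-reported score that could be influenced by allocation is a weaker covariate.

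**Working it through.** **Inputs.** Margin 20 mm, SD 30 mm, one-sided alpha 0.025 and power 80% ({14}); allocation 1:1 ({8}). The correlation ρ between baseline VAS and maximal procedural VAS is not in the documents, so it is assumed over 0.1 to 0.5.

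**The plan's own figure.** With a true difference of zero, n per arm = 2 × SD² × (1.96 + 0.8416)² / margin² = 2 × 900 × 7.849 / 400 = 35.3, rounded up to 36, so 72 in total. Allowing 5% attrition, 72 / 0.95 = 75.8, so 76. Both stated figures reproduce for the unadjusted analysis.

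**Unadjusted power and precision at 36 per arm.** Standard error = 30 × √(2/36) = 7.07 mm. The noncentrality is 20 / 7.07 = 2.83 on 70 degrees of freedom, which gives power of 79.7% (80.7% by the normal approximation). The 95% half-width is 1.994 × 7.07 = 14.1 mm.

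**With baseline VAS as a linear covariate.** Residual SD = 30 × √(1 − ρ²), with one degree of freedom spent (69 left). The equivalent unadjusted sample is 72 / (1 − ρ²).

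| Assumed ρ | Residual SD (mm) | Half-width (mm) | Power | Equivalent N |
|---|---|---|---|---|
| none (unadjusted) | 30.0 | 14.1 | 79.7% | 72 |
| 0.1 | 29.8 | 14.0 | 80.0% | 73 |
| 0.2 | 29.4 | 13.8 | 81.2% | 75 |
| 0.3 | 28.6 | 13.5 | 83.2% | 79 |
| 0.4 | 27.5 | 12.9 | 86.1% | 86 |
| 0.5 | 26.0 | 12.2 | 89.6% | 96 |

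**Cost of estimating the slope.** Chance imbalance in baseline inflates the variance of the adjusted difference by about 1.5% on average (1/68). Multiplying the squared standard error by 1 + 1/68 gives power of 79.5% at ρ = 0.1 and 80.7% at ρ = 0.2. The break-even correlation is then about 0.12; below it, adjustment gains nothing on average. At ρ = 0 the same calculation gives 79.1%, so the worst case is a loss of about 0.6 percentage points.

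**Timing.** Table 2 puts the baseline score before Allocation. Outcomes {12} puts it immediately before the block. The Screening column also carries a pre-intervention timepoint label, which is compatible with the text, but the position of the mark relative to Allocation is not.

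**The case against.** The strongest reply is that nothing in {20a} is wrong. An unadjusted comparison in a randomised trial is unbiased, and this one agrees with the SD used for sizing. A reader might infer that the trial is underpowered for want of the covariate. It is not: 72 and 76 reproduce on the plan's own assumptions.

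A reader might also infer that precision is certainly being lost. The documents do not support that either. The size of any gain rests on a correlation they do not report, and there are grounds to expect a low one. The outcome is pain during reduction under a regional block, {14} cites a median of 5 mm with Bier block, close to the floor of the scale, and {11d} permits other analgesia. At 0.1 to 0.2 the gain runs from nil to about 1.5 percentage points.

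Two further replies have some force. The article does not say that covariates are excluded, and an analysis plan that is not shown may name them. Adding a covariate also needs a rule for missing baseline scores, because {20c} keeps everyone with complete primary outcome data and a careless adjusted model would drop some of them.

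Two smaller inferences should also be avoided. The sentence in {12} about checking that the groups are similar concerns analgesia given before the procedure, not baseline VAS. A between-arm comparison of baseline pain follows only from the general sentence in {20a} on continuous secondary outcomes. Nor does the text state that baseline is taken after randomisation; it only implies a later moment than Table 2 shows.

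All of this limits the point to an improvement. It does not remove it: the variable is already planned, the potential gain far exceeds the potential loss, and the timing and labelling do need tidying.

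**Conclusion.** The point holds as a low-cost improvement, not as an error. Under the plan's SD and margin, with 36 per arm and a true difference of zero, prespecified adjustment would change power from 79.7% to between about 80.0% (ρ = 0.1) and 89.6% (ρ = 0.5), and the half-width from 14.1 mm to between 14.0 and 12.2 mm. These figures assume a linear relation with the same slope in both arms and the stated ρ; the first two values fall by about half a point once slope estimation is allowed for. The true correlation is unknown and may lie at the low end.

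The timing discrepancy is real but modest. It matters mainly because baseline VAS is a clean covariate only if it is recorded before the participant learns the allocation. Listing baseline pain as an outcome is loose labelling with no effect on the primary conclusion.

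**What to change.** 1. In {20a}, specify the primary model as maximal pain VAS on group allocation plus baseline VAS as a linear term, and base the non-inferiority interval on the adjusted difference. Use the same form for one-hour pain. Report the unadjusted estimate as a sensitivity analysis.
2. Keep participants with a missing baseline score by simple imputation, for example the mean of all observed baseline scores, computed without regard to arm or outcome.
3. Reconcile Outcomes {12} with Table 2 so that both record baseline VAS before allocation is revealed.
4. Move baseline pain from the secondary outcomes (abstract and {12}) to the baseline characteristics.

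The change is to wording, with no new measurement and no change in sample size. It costs one degree of freedom and the small variance inflation shown above. It should be settled before any outcome data are seen, because choosing between adjusted and unadjusted results afterwards would weaken a conclusion that rests on one confidence bound.

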**Discussion:**

Existing evidence suggests UGSCB is effective when performed in the operating theatre by trained anaesthetists. SUPERB will be the first randomised controlled trial to elucidate the effectiveness and safety of UGSCB in the ED. The findings have the potential to provide an alternative safe and effective option for the management of upper extremity emergencies in the ED.

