### Provisions for post-trial care {30}

Following closed reduction, the injured part will be typically immobilised with plaster of paris with repeat x-rays performed to assess anatomical alignment of the injured part. After adequacy of reduction, the participant will be discharged from the ED with orthopaedic follow-up within approximately one week for review and ongoing management. In the event where there is inadequate reduction or neurovascular injury requiring urgent treatment, participants will be managed by the acute orthopaedic service. In the event where a participant experiences adverse effects from either BB or UGSCB, they will be managed appropriately by the treating emergency physician in the ED. The type and severity will be compared between groups.

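### At 38 per arm, the general logistic regression rule will often give no estimable odds ratio for rare or technique-specific harms, and three parts of the protocol disagree on when adverse events are collected

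*Protocol article*

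**What the plan says.** **Method.** Statistical methods {20a} states: "Odds of dichotomous outcomes will be compared using logistic regression modelling". It sets no other model for binary outcomes and makes no distinction by how common an outcome is. The same section also summarises categorical variables as counts and percentages.

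**Harms.** Outcomes {12} lists adverse events as a secondary outcome. Provisions for post-trial care {30} says of adverse effects: "The type and severity will be compared between groups". Table 3 lists potential harms by technique, some under one technique only. Section {22} commits to reporting every harm. The abstract presents safety as a main contribution: "SUPERB will be the first randomised controlled trial to elucidate the effectiveness and safety of UGSCB in the ED".

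**Collection window.**
- Outcomes {12} plans an email contact at 24–72 h "after discharge from the ED to evaluate any adverse events post-discharge".
- Table 2 (Participant timeline {13}) marks adverse events in the ED discharge column and leaves the post-discharge column blank for that row.
- Section {18b} says that collection of primary and secondary "outcome data will occur before, during and after the allocated intervention and closed reduction during the index ED presentation", together with routine records of that presentation.

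**The concern.** Two separate matters are involved.

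First, the trial is sized for a pain score, so each arm is small for uncommon events. If a listed harm occurs in one arm and not the other, the fitted log odds ratio runs off to infinity and its Wald interval carries no information. If it occurs in neither arm, there is no odds ratio to estimate. A between-group comparison of that harm then needs some other method. Readers also need to know how high a rate a zero count still allows, given the weight the article puts on safety.

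Second, Table 3 includes infection and nerve injury, which may not be evident when the patient leaves the ED. Whether such events are counted depends on which of the three statements about timing is followed. Section {18b} also argues that attrition will be low because data come from the same clinical event as recruitment. That argument does not carry over to an email sent after discharge.

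**Working it through.** **Arm size.** Inputs from Sample size {14}: "Assuming a non-inferiority margin of 20 mm difference in the mean VAS pain score", with "expected standard deviation of 30 mm [9], alpha 0.025 and a power of 80" per cent. Taking alpha as one-sided and the true difference as zero:

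- n per arm = 2 × 30² × (1.960 + 0.842)² / 20² = 35.3, rounded up to 36. This gives 72 in total and agrees with the protocol: "we would require primary outcome data for 72 participants".
- 72 / 0.95 = 75.8, rounded up to 76, or 38 per arm. The protocol's figure is reproduced.

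**Chance of an empty arm.** For a true rate p in both arms and n per arm:

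- P(no event in a given arm) = (1 − p)^n
- P(at least one arm empty) = 1 − [1 − (1 − p)^n]²
- P(both arms empty) = (1 − p)^(2n)

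The document gives no event rate; Background {6a} only describes complications of the supraclavicular block as relatively infrequent. The rates below are therefore an assumed range.

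| True rate, both arms | Given arm empty (n = 38) | At least one empty (n = 38) | Both empty (n = 38) | At least one empty (n = 36) |
|---|---|---|---|---|
| 0.5% | 83% | 97% | 68% | 97% |
| 1% | 68% | 90% | 47% | 91% |
| 2% | 46% | 71% | 22% | 73% |
| 3% | 31% | 53% | 10% | 56% |
| 5% | 14% | 26% | 2% | 29% |
| 8% | 4% | 8% | <1% | 10% |
| 10% | 2% | 4% | <1% | 4% |

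The chance passes 50% at a rate of about 3.2% with 38 per arm (3.4% with 36). With unequal rates and 38 per arm, it is 73% for 1% against 5%, 47% for 2% against 10%, and 16% for 5% against 10%.

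**Technique-specific harms.** Table 3 lists lung puncture and phrenic nerve paralysis for the supraclavicular block only, and cuff discomfort and methaemoglobinaemia for the Bier block only. If such a harm can arise only from its own technique, the other arm is empty whatever the rate, except through patients who also receive the other block, which section {11b} permits.

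**What the model does.** Take 0/38 against 3/38. After 5, 10, 20 and 30 iterations the maximum-likelihood log odds ratio is −4.1, −9.1, −19.1 and −29.1, with standard errors of 2.7, 32, 4.7 × 10³ and 7.0 × 10⁵. It does not converge. On the same data:

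- Risk difference 0 − 3/38 = −7.9 percentage points, Newcombe 95% interval −20.8 to +2.6.
- Firth-type odds ratio (0.5 added to each cell) = (0.5/38.5) / (3.5/35.5) = 0.13.
- Fisher's exact p = 0.24.

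With both arms empty, the Firth-type ratio is (0.5/38.5) / (0.5/38.5) = 1 by construction, so only counts and limits are informative.

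**What zero events allows.** The exact two-sided 95% upper limit for 0/38 is 1 − 0.025^(1/38) = 9.3%.

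**Window, side by side.** Outcomes {12} seeks adverse events after discharge. Table 2 has a post-discharge column and uses it for transfers, later sedations and operations, but not for adverse events. Section {18b} puts primary and secondary outcome collection within the index presentation. It therefore disagrees with Outcomes {12} on the email, and with both Outcomes {12} and Table 2 on later procedures. All three are current text.

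**The case against.** The strongest reply is that {20a} states an ordinary default and does not name adverse events. A comparison of type and severity is not itself a binary outcome, the term logistic regression does not exclude exact or penalised forms, and the handling of empty cells is commonly left to an analysis plan, which is not shown here. This largely stands: the absence of a sparse-data rule is not an error in itself. What remains is that {20a} is the only method given for binary comparisons, that any per-harm or any-event comparison would fall under it, and that its ordinary form fails on foreseeable data.

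A reader might infer that the trial will have nothing usable on harms. The document does not support that: counts and percentages are planned in {20a}, and {22} commits to reporting all harms. Nor can one infer that empty arms are likely for binary outcomes in general. No rates are given, and an any-event composite that includes injection pain, bruising or cuff discomfort may be common enough for logistic regression to work well. Sedation, block failure and transfers are likewise not shown to be rare. Replacing odds ratios by risk differences throughout would be a preference.

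On the window, it is fair to say that the blank cell in Table 2 looks clerical, that {18b} is a general statement about retention, and that Outcomes {12} gives an explicit instruction. A reader might conclude that delayed events will be missed. That would follow only if staff worked from the table and disregarded the outcome definition. The inconsistency is nevertheless in the text.

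**Conclusion.** The point holds in a limited form. For individual harms with a true rate of about 3% or less in each arm, at least one arm will more likely than not be empty at 38 per arm, and the ordinary odds ratio cannot then be estimated. The same applies to harms confined to one technique. The 3% figure is an assumption about rates, since the document supplies none. At 5% the chance is 26%, at 10% it is 4%, and logistic regression is then usually serviceable. Applying {20a} to adverse events is a reasonable inference, not something the protocol states.

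The conflict over the adverse event window rests on no assumption and needs reconciling. It is a separate consistency matter and does not add weight to the modelling point. Both concern secondary and safety outcomes; the primary non-inferiority conclusion is untouched.

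**What to change.** 1. Keep logistic regression for binary outcomes that are not sparse.
2. Add a sentence, in the protocol or the analysis plan, for outcomes with an empty or sparse cell: Firth or exact logistic regression, or a risk difference with a Newcombe or Miettinen-Nurminen 95% interval. Choose the method and define what counts as sparse before the data are seen.
3. Report technique-specific harms, and harms absent from both arms, as counts with exact 95% limits per arm, so that a zero count is shown with its upper limit (9.3% for 0/38).
4. Mark adverse events in the post-discharge column of Table 2, and bring {18b} into line with Outcomes {12}.
5. Report post-discharge events together with the number who answered the email. The document states no denominator for these events.

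The cost is a few lines of text. The email contact is already planned, so no new data are needed. The small drawback is that sparse outcomes will be reported with a different method or effect measure from the other binary outcomes.
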